Previous work has allowed understanding a part of the inter-patient variations in terms of dose-response of TAC and mycophenolic acid (MPA), the active metabolite of MMF. The influence of patient’s genetic profile can explain part of the observed PK variability.^17^ For instance, patients presenting different *CYP3A5* phenotypes show an important shift in TAC metabolism which accounts for approximately 50% of the observed dose-requirement variation and has led to the abovementioned CPIC genotype-based dosing guidelines. For MPA, variants in *UGT1A9* and *ABCC2* have been associated with differences in PK parameters without clear pharmacogenetic testing guidelines or interpretation.^9^ Other factors of inter-patient variations include age at transplantation, co-medications, body surface area and others.^9 17^ More recently, the gut microbiota composition has been shown to be an important factor of inter-individual PK variability.

The importance of the gut microbiome for explaining the fate of immunosuppressive drugs in the organism has been largely understudied although it is now widely accepted that the complex ecosystem of intestinal microbes dynamically takes part in several functions of the host beyond digestion, including drug metabolism.^18^,^22^ Indeed, the gut microbiota synthesises numerous compounds that may interact with and affect the human host metabolome. Not only gut microorganisms express numerous enzymes able to directly metabolise xenobiotics^23^ but they are also able to control the host PK phenotype through different undirect processes.^24^ Inter-individual differences in PK profiles might thus be explained by between-subject differential microbiota composition or function. Moreover, contrarily to the host genetic make-up, the microbiota is not inflexible and might thus be a source of intra-individual variability. Microbiota composition is in fact affected by many environmental factors such as diet, lifestyle, age, physiological status and pharmaceuticals.^25 26^ Studies have highlighted differences in gut microbiota composition of transplanted patients compared with healthy patients,^27^,^29^ with significant changes also observed in the microbiome of patients’ pre-transplantation samples compared with post-transplantation samples,^30^,^32^ indicating a potential interplay between microbiota, transplant status and immunosuppressive pharmacotherapy.

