## Hypothesis and objectives

The hypothesis of the trial is that the gut microbiota composition, by inducing physiological changes, is influencing both the oral absorption of TAC and the entero-hepatic recirculation of MPA, thereby impacting on their PK profile, and possibly explaining the variability in the treatment response.

The primary aim of the ENIGMA trial is to identify staging biomarkers of TAC and MMF PK variability by investigating the gut microbiota modulations and physiological changes following kidney transplantation. Additionally, the trial seeks to link PK variabilities, microbiome changes overtime (metabolic and compositional) and responses to immunosuppressive therapy (such as graft survival/rejection and drug-related toxicities). Given the common use of antibiotics in this population, the study will also assess the effect of antibiotherapy interventions on the microbiota composition and the subsequent consequences on immunosuppression pharmacotherapy.

As a secondary endpoint, the study will also explore whether the genotype of the donor and the recipient can predict PK variabilities. Furthermore, it will analyse the response to therapy and related physiological changes from a molecular perspective (ie, transcriptomics, metabolomics and proteomics). Ultimately, this trial aims to link gut microbiota changes and PK variabilities to other blood and urinary-omics data to evaluate their potential as biomarkers and elucidate the underlying mechanisms of the arising observations.

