### Sample size calculation

Power calculation indicates that a sample size of 50 patients with nine repeated PK measurements will provide an 80% statistical power considering a type I (alpha error) of 5% to detect clinically relevant results. The power to detect true associations strongly depends on effect size, heterogeneity of the background noise and sample size. The noise signal is limited by (i) anticipating baseline measurements, (ii) selecting living-donor recipient (limits the variability in phenotypes), (iii) monitoring the individuals over a long period of time (ie, 12 months) and (iv) detaching the interoccasion from the intraoccasion variability.

Considering an SD of 57.5 ng/mL per mg/kg in the TAC dose requirement (preliminary data) and a repeated measurement design with 9 PK time points, a power of 0.8 (1-β = π=80%) can be guaranteed to detect a Δmean as low as 17.25 ng/mL per mg/kg across the levels of a tested-independent variable with a typical type I (α) error of 0.05 (ie, effect size=0.30) which correspond to an average ΔCmin of 2.6 ng/mL considering a typical standard dose (ie, 0.15 mg/kg). This difference can be considered as clinically relevant (therapeutic target 7–20 ng/mL).

Considering a SD of 2.6 µg/mL in the MPA concentrations for a typical dose of 1000 mg (preliminary data) and a repeated measurement design with 9 PK time points, a power of 0.8 (1-β = π=80%) can be guaranteed to detect a Δmean as low as 0.78 µg/mL across the levels of a tested independent variable with a typical type I (α) error of 0.05 (ie, effect size=0.30). Considering that the range of MPA exposure varies between ±2 to 10 µg/mL depending on the time post-dose, this difference can also be considered as clinically relevant.

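### The guaranteed 80% power rests on settings the protocol does not fix, and for predictors fixed within a patient it can fall well below 80%

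*Protocol article*

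**What the plan says.** The section Sample size calculation of the protocol article opens by stating that "a sample size of 50 patients with nine repeated PK measurements will provide an 80% statistical power" at a type I error of 5%. It then makes the claim specific to each drug.

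- **Tacrolimus:** the SD of dose requirement is taken from preliminary data as 57.5 ng/mL per mg/kg. On that basis 80% power "can be guaranteed to detect a Δmean as low as 17.25 ng/mL per mg/kg across the levels of a tested-independent variable". The section labels this as an effect size of 0.30 and sets α at 0.05.
- **Mycophenolic acid:** the same claim is made for a difference of 0.78 µg/mL against an SD of 2.6 µg/mL.

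In both cases 0.30 is the difference divided by the SD. The section names no test, number of levels or within-patient correlation, and does not say whether the tested variable differs between patients or changes within them.

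Two other places bear on the point. The Introduction says that CYP3A5 phenotype "accounts for approximately 50% of the observed dose-requirement variation" for tacrolimus. Hypothesis and objectives says that the study will, as a secondary endpoint, "explore whether the genotype of the donor and the recipient can predict PK variabilities".

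**The concern.** Nine measurements on one patient are not nine independent observations. For a predictor that is constant within a patient, such as genotype or a baseline microbiota class, repeated measurements add less information as the within-patient correlation rises. With f held fixed, power also falls as the number of levels rises. A power that is guaranteed across the levels of any tested variable cannot hold without values for these settings.

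What is at stake is how n = 50 is justified and how null results are read. A negative genotype or baseline-microbiota finding could be reported as coming from a test with 80% power when the real figure was much lower.

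**Working it through.** **Inputs from Sample size calculation:** N = 50 patients; m = 9 measurements, taken as stated; α = 0.05; effect size 0.30; 17.25/57.5 = 0.30 and 0.78/2.6 = 0.30.

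**Assumed, because not given:** an F test (two-sided), a common within-patient correlation ρ, and k levels of the predictor.

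**Formula for a between-patient predictor:** noncentral F with k − 1 and N − k degrees of freedom and λ = N·f²·m / (1 + (m − 1)ρ).

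**Step 1. Reproduce the stated 80%.** With f = 0.30, k = 2 and ρ = 0.5:

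λ = 50 × 0.09 × 9 / (1 + 8 × 0.5) = 40.5 / 5 = 8.10, which gives power 79.6%.

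This is a back-fit, and other pairs do as well. Three levels at ρ = 0.37 give 79.8%, and four levels at ρ = 0.30 give 80.1%.

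**Step 2. Vary the unstated settings, with 0.30 as Cohen's f.**

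| ρ | λ = 40.5/(1 + 8ρ) | Power, 2 levels | Power, 3 levels |
|---|---|---|---|
| 0.4 | 9.64 | 86.1% | 77.3% |
| 0.5 | 8.10 | 79.6% | 69.4% |
| 0.6 | 6.98 | 73.5% | 62.4% |
| 0.7 | 6.14 | 68.0% | 56.5% |
| 0.8 | 5.47 | 63.0% | 51.5% |

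**Step 3. Use the effect size as the protocol derives it.** For two equal groups, f is half the standardised difference. A difference of 17.25 with SD 57.5 therefore has f = 0.30/2 = 0.15. Then λ = 50 × 0.0225 × 9 / (1 + 8ρ) = 10.125/(1 + 8ρ).

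| ρ | λ | Power, 2 levels |
|---|---|---|
| 0 | 10.13 | 87.7% |
| 0.03 | 8.17 | 80.0% |
| 0.1 | 5.63 | 64.2% |
| 0.3 | 2.98 | 39.4% |
| 0.5 | 2.03 | 28.6% |
| 0.7 | 1.53 | 22.9% |

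Conversely, f = 0.30 in two equal groups is a difference of 0.60 SD. That is 0.60 × 57.5 = 34.5 ng/mL per mg/kg for tacrolimus and 0.60 × 2.6 = 1.56 µg/mL for mycophenolic acid, twice the stated differences. The tacrolimus differences detectable with 80% power between two equal groups are 34.7, 37.3, 39.8 and 42.2 ng/mL per mg/kg at ρ = 0.5, 0.6, 0.7 and 0.8.

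**Step 4. Predictors that vary within patients.** Here the correlation works the other way, because the error variance is proportional to 1 − ρ. Take a binary predictor split evenly over each patient's nine measurements, with difference/SD = 0.30:

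SE = √[(1 − ρ)(1/4.5 + 1/4.5)/50], and power = Φ(0.30/SE − 1.96).

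This gives 88.9% at ρ = 0, 96.7% at 0.3 and 99.4% at 0.5.

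A within-patient factor over the nine occasions (λ = N·f²·m/(1 − ρ), 8 and 392 degrees of freedom) with f = 0.15 gives 58%, 77%, 91% and 99% at ρ = 0, 0.3, 0.5 and 0.7. With f = 0.30 it exceeds 99% throughout.

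**Step 5. What the document says about ρ.** If the 50% attributed to CYP3A5 is a share of total variance, a patient-fixed trait alone implies ρ of at least about 0.5 for tacrolimus. The Introduction presents it among factors of inter-patient variation, however. A share of between-patient variance alone would not determine ρ. No comparable share is given for mycophenolic acid.

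**The case against.** **The primary interest is change over time.** The main aim concerns microbiota changes after transplantation, and donor and recipient genotype is secondary. For time-varying predictors a higher correlation helps. This stands and limits the point to between-patient predictors. It does not rescue a guarantee worded for any tested variable.

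**The document does not show that the true settings are unfavourable.** A reader might infer that 80% arises only with two levels and a correlation of 0.5, that the protocol's own figures lie above both, and that the stated power is therefore simply too high. The documents do not support that reading. Other pairs also give 80%, no number of predictor levels appears anywhere, and the percentile classes in Data analysis apply to the PK phenotypes. The CYP3A5 share is suggestive at most, and for tacrolimus only.

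**Covariate adjustment could recover power.** Suppose CYP3A5 did explain half of total variance and the analysis adjusted for it. For another predictor, f would rise from 0.30 to 0.30 × √2 = 0.42. Total correlations of 0.7 and 0.8 would become residual correlations of (0.7 − 0.5)/0.5 = 0.4 and (0.8 − 0.5)/0.5 = 0.6. Two-level power would then be 99% and 96%. CYP3A5 itself would have f = 1.0 and ample power, so it is not an example of the shortfall. This is fair and shows again that power depends on choices the section does not state. It also relies on 0.30 being Cohen's f. Starting from f = 0.15, the same adjustment gives 58% and 45%.

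**An article condenses a fuller protocol.** The correlation and the number of levels may be given there, and their absence alone would be no finding. What remains is a positive statement, made for both drugs, that power is guaranteed. The article's own list of limitations concedes that 50 patients may restrict power.

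**Conclusion.** The point holds in a limited form. The guarantee is unsupported, because the power depends on the within-patient correlation, the number of levels and the type of predictor, and the article fixes none of them.

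For between-patient predictors with 0.30 as Cohen's f, power ranges from 80% down to 63% with two levels (correlation 0.5 to 0.8), and from 69% to 57% with three (correlation 0.5 to 0.7). A correlation below 0.5 would give more than 80% with two levels. With 0.30 as difference/SD in two equal groups, which is how the section obtains it, power is about 29% at correlation 0.5, and 80% requires a correlation near 0.03. On that definition the stated power for between-patient predictors is too favourable at any but a very small correlation.

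These figures assume an F test at α = 0.05, nine measurements from all 50 patients, a common correlation, equal groups where f = 0.15 is used, and no covariate adjustment. The shortfall does not extend to time-varying predictors.

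**What to change.** Keep n at 50 and revise Sample size calculation as follows.

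1. Delete the wording that power can be guaranteed, for both drugs.
2. State the test, and whether 0.30 is Cohen's f or difference/SD. If it is Cohen's f, correct the differences of 17.25 and 0.78 to match.
3. Estimate the within-patient correlation for each drug from the preliminary data that gave the SDs of 57.5 and 2.6.
4. Give a short table of power and detectable difference by correlation and number of levels, separately for between-patient and within-patient predictors.

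The revision should not say that 80% applies only to a two-level predictor at correlation 0.5 or less. That would be wrong for two equal groups 17.25 apart (29% at 0.5), for three levels at correlations up to about 0.37, and for time-varying predictors.

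The cost is one rewritten paragraph and a small table, with no extra patients or samples. The stated power for between-patient predictors is likely to look less favourable.

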### Data management

Patients’ medical data—including demographics, medical history, treatments and laboratory results—are collected from their medical records at the time of inclusion and continuously throughout the entire follow-up period. Both standard-of-care and study-specific data are securely stored using Research Electronic Data Capture, a web-based software platform designed to support data capture for research studies. Access to the platform is restricted to authorised personnel to ensure confidentiality and data integrity. The collected data will be archived for 25 years.

### Data analysis

The different PK phenotypes will be analysed either as continuous variable or categorical variables (classified according to the percentile range). These PK phenotypes include primarily classical PK parameters (clearance, absorption rate, AUC, drug systemic concentrations at a given time point), intra-patient variability index as assessed by the coefficient of variation observed in the dose-adjusted concentrations across the follow-up, for MPA, the metabolite to parent drug ratio, dose requirement (ie, dose adjusted drug exposure), number of dose adjustments needed to achieve stable target levels and time to achieve stable target levels.

### Study discontinuation

Patients will be withdrawn from the trial’s follow-up if they enter one or more of the conditions mentioned in box 2.

Box 2Conditions for patient withdrawal from ElucidatiNg Immunosuppressant pharmacokinetic variabilities by investigating Gut Microbiome modulations After kidney transplantation (ENIGMA) trial
**Conditions for patient withdrawal from ENIGMA**
PregnancyImmunosuppressive therapy switch during follow-up (for any reasons)At the end of follow-upVoluntary discontinuationSuspected noncomplianceDeathGraft loss

Data collected before patient withdrawal or discontinuation will be kept and included in the data analysis unless not authorised by the patient or suspected to confound the results. No additional data will be generated after patient withdrawal and his/her follow-up will be stopped.

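### Data collected before withdrawal may be left out on suspicion of confounding, with no objective criterion and no time limit on the decision, so selection related to the outcome is possible

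*Protocol article*

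**What the plan says.** The protocol article's Study discontinuation section, with Box 2, lists when follow-up stops. The reasons include suspected noncompliance, a change of immunosuppressive therapy for whatever reason, graft loss and death. It then sets a default for data already in hand: "Data collected before patient withdrawal or discontinuation will be kept and included in the data analysis". Two exceptions follow: "unless not authorised by the patient or suspected to confound the results".

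The article does not say what counts as confounding, who decides, or when the decision falls relative to the analyses.

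Two other sections bear on this:

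- Data analysis lists, among the PK phenotypes, an "intra-patient variability index as assessed by the coefficient of variation observed in the dose-adjusted concentrations across the follow-up". It also lists the number of dose adjustments and the time to stable target levels.
- Hypothesis and objectives sets out to link PK variability and microbiome change to "responses to immunosuppressive therapy (such as graft survival/rejection and drug-related toxicities".

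**The concern.** The patients exposed to the exception are those who left the study, and several reasons for leaving are close to the quantities under study. Irregular intake raises the variation of dose-adjusted concentrations, which is one of the phenotypes. A therapy switch may follow toxicity or an exposure problem. Graft loss is itself a response outcome. A rule that removes such patients on suspicion can therefore remove them because of their outcome.

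The test is also an awkward one. A confounder is normally measured and adjusted for, or examined in a sensitivity analysis. Here, data judged to disturb the results may simply be left out.

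With 50 patients, a few exclusions can change whether a biomarker association is declared. Removing genuine high values weakens true associations. Removing patients who do not fit a pattern creates or strengthens one, and removing those who fit it does the reverse.

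**Working it through.** **Inputs from the article (Sample size calculation).** N = 50, nine PK measurements, 80% power and a 5% type I error. The TAC figures are an SD of 57.5 and a detectable difference "as low as 17.25 ng/mL per mg/kg", so 17.25 / 57.5 = 0.30. For MPA, 0.78 / 2.6 = 0.30.

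**Inputs assumed.** A two-sided test; 5 or 10 withdrawn patients; 1 to 3 of them removed; a loss of 10% or 15% of outcomes. The article gives no withdrawal or exclusion rate.

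**Step 1: the plan's own figure.** The article states that "a sample size of 50 patients with nine repeated PK measurements will provide an 80% statistical power". Take 0.30 as Cohen's f for a between-patient factor with two levels and a within-patient correlation of 0.5 (both assumed):

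λ = f²·N·m / (1 + (m − 1)ρ) = 0.09 × 50 × 9 / (1 + 8 × 0.5) = 40.5 / 5 = 8.1.

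The noncentral F distribution with 1 and 48 degrees of freedom gives power of 79.6%, against the stated 80%. The figure is reproduced on that reading. It includes no allowance for selective exclusion.

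**Step 2: losing the high end of a genuine outcome.** Let biomarker x and phenotype y be standard normal with slope β. Keep only y below its (1 − q) quantile c. With h = φ(c) / (1 − q), the retained variance of y is v = 1 − c·h − h², and the slope becomes β·v / (1 − β²(1 − v)).

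- q = 10%: c = 1.2816, h = 0.1755 / 0.90 = 0.195, v = 1 − 0.250 − 0.038 = 0.712. The slope ratio is 0.712 / (1 − 0.09 × 0.288) = 0.73 for β = 0.3, and 0.712 / (1 − 0.16 × 0.288) = 0.75 for β = 0.4.
- q = 15%: c = 1.0364, h = 0.2332 / 0.85 = 0.274, v = 1 − 0.284 − 0.075 = 0.640. The ratio is 0.66 for β = 0.3 and 0.68 for β = 0.4.

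Simulation with n = 50 agrees: 0.735 and 0.749 at 10%, and about 0.66 to 0.68 at 15%. The slope shrinks by about a quarter to a third. For β = 0.3, power in this simple model falls from about 57% to about 40% when the top 10% is lost.

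Under β = 0, the same exclusion leaves the slope at zero and the error rate at about 5%. Selection on the outcome alone does not create false positives.

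**Step 3: adversarial removal under the null.** With n = 50 and a true slope of 0, only randomly withdrawn patients can be removed, and the ones removed are those that most weaken the association. Rejection rates at nominal 5%:

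| Withdrawn | 1 removed | 2 removed | 3 removed |
|---|---|---|---|
| 5 | 7.5% | 9.0% | 7.6% |
| 10 | 8.5% | 10.3% | 12.4% |

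A repeat run, with each removal in the direction already observed, gave 6.7%, 7.7% and 7.3% for five withdrawn, and 8.3%, 10.6% and 12.3% for ten. A fixed-direction version (5 of 10 withdrawn patients dropped) gave 7.1%, with mean slopes of +0.07 or −0.07 depending on which patients go.

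**Step 4: direction when an association exists.** With a true slope of 0.30 and 5 of 10 withdrawn patients dropped, the mean slope is 0.36 if discordant patients go and 0.24 if concordant patients go. Random exclusion leaves it at 0.30.

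**The case against.** **Noncompliance can be an artefact.** A concentration divided by a dose that was not taken is measurement error, not PK. Suppose 5 of 50 patients have an outcome unrelated to the biomarker and shifted by 1.5 to 2.5 SD, with a true slope of 0.35 (all assumed). Keeping them gives a slope of about 0.31 to 0.32 and power of 43% to 54%. Dropping them gives 0.35 and about 67%. In that case exclusion removes bias. This stands: Step 2 applies only if the removed values are genuine variability, and keeping everything in the main analysis without qualification is not clearly better.

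**The article is a condensation.** It cites a third protocol version that is not shown, and criteria may be set out there or in an analysis plan. This stands in part. Missing operational detail would be no fault, but the article states a rule that allows removal on suspicion.

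**Stronger readings.** A reader might infer that exclusions will be decided with the PK and microbiome results known. The article gives no timing; it only fails to rule this out. A reader might also infer that low or erratic levels are what triggers suspected noncompliance. The article does not say how it is detected, and the medication questionnaire that accompanies each faecal sample (Study design) is another possible source. Finally, letting any of the 50 patients be removed gives error rates of about 13%, 24% and 37% for one, two or three removals. The clause concerns data from before withdrawal or discontinuation, so those rates describe a different rule. Box 2 does list the end of follow-up among its conditions, but treating completers as withdrawn on that basis strains the text.

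**Conclusion.** The concern holds in limited form. As written, the rule lets authorised pre-withdrawal data be left out on an undefined suspicion, for patients whose reasons for leaving overlap with the phenotypes and responses analysed. That permits selection related to the outcome; it does not show that such selection will occur.

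The actual bias has no derivable size or sign. The illustrations bound it under stated assumptions: a slope reduced by about a quarter to a third if the top 10% to 15% of genuine values is lost, and a 5% error rate raised to about 8–12% by adversarial removal of one to three patients from five to ten withdrawn. The second effect needs selection that depends on biomarker and outcome together.

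Severity is should-fix. Inclusion is the default, the exception reaches only withdrawn patients, and the study is a single-centre biomarker search that already declares its limited sample size.

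**What to change.** In the Study discontinuation section, keep the consent exception and replace the confounding exception with a rule to this effect:

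- All authorised data collected before withdrawal are kept.
- Occasions affected by suspected noncompliance are flagged by objective criteria fixed before the PK and microbiome data are linked.
- Results are reported with and without the flagged occasions, and the version that serves as the main analysis is named in advance.

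If the full protocol already holds such criteria, the article need only refer to them. The choice of main version can go either way, given the artefact argument, provided it is made before linkage.

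The cost is one sentence and one extra analysis. No visit, sample, withdrawal condition or treatment decision changes. Recruitment began in September 2024, so the change should be made before the data are linked.
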